### Study endpoints

#### Primary endpoint

It is assumed that patients who suffer acute SCI regain more of their motor and sensory functions because of treatment with EWST than patients in the control group. Six months after the baseline measurement, patients will be invited for a follow-up visit as soon as possible. The primary endpoint will be a composite endpoint composed of the ISNCSCI subscores — motor and sensory function — to achieve the required power of the study with the expected incidence. These subscores and all secondary endpoints will be analyzed descriptively to provide further insight or to derive hypotheses as appropriate.

The primary composite endpoint is calculated as the difference between the upper and lower extremities motor score (ULMS + LLMS), light touch (LT), and pin prick (PP) at two points in time.

delta.TMSC = TMSC_after 6 months_ minus TMSC_at baseline_

TMSC = Total motor and sensory score

#### Secondary (exploratory) endpoints and control variables

AIS classificationDegree of spasticity according to Penn Spasm Frequency ScaleWalking abilityWISCI II (Walking Index for Spinal Cord Injury II)TUG (Timed Up and Go Test)10-m timed walk6-min walk testUrological functionHand motor functionPlantar reflexIndependence in everyday life of patients is assessed with the Spinal Cord Independence Measure (SCIM II)The number of study-related adverse events (AEs) are measured according to NCI CTCAE, version 5.0

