**Methods:**

This two-arm three-stage adaptive, prospective, multi-center, randomized, blinded, placebo-controlled study has been initiated in July 2020, and a total of 82 patients with acute traumatic SCI will be recruited for the first stage in 15 participating hospitals as part of a two-armed three-stage adaptive trial design. The focused ESWT (energy flux density: 0.1–0.19 mJ/mm^2^, frequency: 2–5 Hz) is applied once at the level of the lesion, five segments above/below, and on the plantar surface of both feet within the first 48 h after trauma.

The degree of improvement in motor and sensory function after 6 months post-injury is the primary endpoint of the study. Secondary endpoints include routine blood chemistry parameters, the degree of spasticity, the ability to walk, urological function, quality of life, and the independence in everyday life.

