## Methods

This is a two-arm three-stage adaptive, prospective, multi-center, randomized, blinded, placebo-controlled clinical trial according to the MPG (Medizinproduktegesetz [Medical Devices Act]) which is designed as a two-arm three-stage adaptive trial.

Fourteen treating hospitals and three rehabilitation centers in Austria and Germany will participate. The allocation of the study groups will occur by means of a block randomization, in order to guarantee the best possible balance between the treatment group, the control group, and the treating hospitals. The study groups are comprised of a treatment group (extracorporeal shock wave therapy by means of electrohydraulic shock wave generation) and a control group (placebo ESWT).

To gain as homogenous groups as possible, a stratified block randomization with a block size of four will be done. The assignment to treatment and placebo group will be made in a ratio of 1:1. For stratification, three different neurological levels of injury will be used:
Cervical injuries: C1–C8Thoracic and lumbar injuries (T1–L1)Peripheral nervous system injuries (cauda equina and conus medullaris syndromes [35]; L2–S5)

Recruitment of patients takes place continually at admission to acute care in one of the 14 participating hospitals (13 in Austria, 1 in Germany). Patients and assessors of study relevant data are blinded to group allocation. The operating room staff and persons involved in the application of the study intervention are not blinded to group allocation and are required to keep it as a secret.

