#### Blinding and unblinding

The study will be blinded for treatment so that the patient and the assessor of the neurological assessment and gait analyses are unaware of the treatment group assigned. The randomization list will be opened after the study database has been locked.

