### Statistics

#### Study sample size

Sample size calculation is usually based on an effect size expected from a given treatment. Due to a lack of knowledge about the effects of EWST on sensory (SF) and motor functions (MF), such an estimation is limited. For this reason, a so-called adaptive design was chosen, corresponding to the “multi-arm multi-level approach” (MAMS approach) proposed by Jaki et al. [65]. The advantage of this design is that the effect size needed to calculate the sample size is not based on specific values, but on probabilities (*p* and p0) that can be used to identify the desired or the uninteresting effect. The probability *p* = 0.6 chosen for the study for the desired effect means that a randomly selected person in the treatment group has a 60% probability of achieving a better result than a randomly selected person in the control group. The uninteresting effect is assumed with a probability of p0 = 0.5. This value means that both the novel treatment and the placebo treatment perform equally well (Jaki et al., 2019). Another advantage of MAMS is that this form of sampling does not require any knowledge of the variance of the endpoint variables. All the calculations required for this are implemented in an R package and published accordingly (Jaki et al., 2019).

A two-armed, three-stage adaptive study design is envisaged at Neurowave. In stage 1 and stage 2, interim evaluations are carried out to determine whether the study can already be terminated. This will be the case if either the intended and thus desired result can already be sufficiently confirmed, or it becomes apparent that the study will not be a success. These interim evaluations offer the opportunity to shorten the study. If none of these two cases occur, the study will continue up to stage 3. The overarching advantage of this design is that the smallest possible number of patients can be found to demonstrate a medically relevant effect.

With a one-sided error rate of 5% and a planned power of 80%, the following design parameters could be calculated. For the upper and lower limits, the triangle test is selected [65].

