## Trial status

Recruitment of study participants started in November 2020. Since then, recruitment takes place on an ongoing basis by admission of patients with acute spinal cord injuries. For patients who are included in the study, the follow-up phase after the baseline assessment will take approximately 6 months.

A planned interim analysis will be carried out after 41 patients have been included in each of both groups and all follow-up examinations have been completed. A further interim analysis will be planned after 82 patients per group. With unexpected major effects, the study will be prematurely terminated or, with low chances of success, will be canceled. An unplanned interim analysis will take place, should adverse events or side effects occur.

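### The only adverse-event endpoint counts events judged study-related, so the safety comparison between arms rests on a causality judgement that randomisation and the sham make unnecessary

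*Protocol article*

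**What the plan says.** Under Study endpoints, the section Secondary (exploratory) endpoints and control variables ends with its only safety item: "The number of study-related adverse events (AEs) are measured according to NCI CTCAE, version 5.0". No item in that list covers all adverse events, or serious adverse events, irrespective of cause. The abstract also names routine blood chemistry among the secondary endpoints ("Secondary endpoints include routine blood chemistry parameters, the degree of spasticity, the ability to walk, urological function, quality of life"), so the item quoted first is the only adverse-event endpoint, though not necessarily the only data bearing on safety.

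The section Primary endpoint sets the analysis: "These subscores and all secondary endpoints will be analyzed descriptively". The later section on secondary endpoints, under Data analysis, allows exploratory tests at the 0.05 level.

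On blinding, Methods says "Patients and assessors of study relevant data are blinded to group allocation" and also "The operating room staff and persons involved in the application of the study intervention are not blinded to group allocation". The section Blinding and unblinding is narrower: "the patient and the assessor of the neurological assessment and gait analyses are unaware of the treatment group assigned". The article does not say who decides whether an event is study-related.

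**The concern.** Allocation is 1:1 and the control group receives the same procedure with a dummy applicator. Apart from chance, a difference between arms in the number of patients with any adverse event is therefore attributable to the active device. The published endpoint discards that advantage by admitting an event only after an individual judgement on cause.

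That judgement is hard in this population. Patients have acute spinal injury, often with injuries to the extremities, and many have surgery. Application of either the device or the sham may extend anaesthesia and require a change of position. Most events will have another plausible explanation. The article's own expectations point the same way: Risks and benefit says that earlier studies showed no adverse events, and the Discussion calls the method free of risk.

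If attribution is incomplete but equal in both arms, a true excess shrinks. If it differs between arms, the difference can shrink, vanish, reverse or appear where none exists. The table that should inform readers about harm in a new use of the device would then depend on something the trial does not measure.

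**Working it through.** No figure in the plan is at issue, so there is nothing to reproduce. The check is a reading of the endpoint, followed by an illustration of what the restriction can do.

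**Reading.** The endpoint is defined by attribution, so an event judged unrelated is excluded by definition. This is a stated choice, not a detail left open. The article's widest blinding statement (Methods) covers assessors of study-relevant data. Its dedicated blinding section names only the patient and the neurology and gait assessor. Blinding of the causality judgement is therefore plausible but not explicitly secured.

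**Inputs.** From the document: 41 per arm at the first interim analysis and 123 per arm at the maximum (table under Study sample size). Assumed, because the document gives no rates: all-cause risk of at least one event 15% control and 30% active; 20% of background events judged study-related; a fraction *f* of the device-caused excess judged study-related, with *f* from 20% to 100%.

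**Formulas.** Counted risk, control: 0.15 × 0.20 = 0.03. Counted risk, active: 0.03 + 0.15 × *f*.

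Power (two-sided 5%) = Φ[(d − 1.96 × se0) / se1], where d is the difference in risk, se0 = √(2 p̄(1 − p̄)/n) with p̄ the mean of the two risks, and se1 = √((pC(1 − pC) + pT(1 − pT))/n).

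All events, n = 123: d = 0.15, p̄ = 0.225, se0 = 0.0533, se1 = 0.0524. Power = Φ[(0.15 − 1.96 × 0.0533)/0.0524] = Φ(0.87) = 0.81.

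Study-related only, *f* = 20%, n = 123: d = 0.03, p̄ = 0.045, se0 = 0.0264, se1 = 0.0264. Power = Φ(−0.83) = 0.20.

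| Count used | Control | Active | Power, 123 per arm | Power, 41 per arm |
|---|---|---|---|---|
| All events | 15% | 30% | 81% | 37% |
| Related, *f* = 20% | 3% | 6% | 20% | 10% |
| Related, *f* = 50% | 3% | 10.5% | 65% | 27% |
| Related, *f* = two-thirds | 3% | 13% | 83% | 38% |
| Related, *f* = 100% | 3% | 18% | 97% | 60% |

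Under these assumptions the restricted count loses power when less than about two-thirds of the excess is attributed to the study, and gains power above that.

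**Other assumed rates, 123 per arm.** With 30% control and 45% active, the true difference is 15 points and the power for all events is 68%. If 20% of events in each arm are judged related, the counted risks are 6% and 9% (about 7 and 11 patients), and power is 14%.

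**Unequal attribution.** With the same 30% and 45%, shares judged related of 20% in control and 10% in active give 0.30 × 0.20 = 6% and 0.45 × 0.10 = 4.5%, so the sign reverses. With equal true risks of 30%, shares of 10% and 20% give 3% and 6%, a difference that does not exist. These two cases show what could happen. Nothing in the document says that attribution will differ by arm.

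**The case against.** Four objections have weight.

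**Unblinded staff.** A reader might infer that operating room staff, who know the allocation, decide which events are study-related. The article does not say so. It says that assessors of study-relevant data are blinded, and staff who know the allocation must keep it secret. What stands is narrower: the dedicated blinding section does not mention adverse-event assessment. On its own that could be a detail left to the full protocol. The main point does not need it, because under-attribution by fully blinded assessors still dilutes a true excess.

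**Unrecorded harms.** A reader might infer that events judged unrelated are lost. The article supports only that they leave this endpoint. Full collection and reporting rules may stand in a protocol or analysis plan that is not shown.

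**Conflict with the interim trigger.** Trial status says "An unplanned interim analysis will take place, should adverse events or side effects occur", with no limit to related events. A reader might call this a contradiction. It is not: a monitoring trigger may properly be wider than an endpoint.

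**Power.** The endpoint is descriptive and no safety test is powered. Restricting to related events can also remove background noise and raise power, as the table shows. This stands. The figures illustrate how far the result depends on attribution. They do not measure a defect of known size.

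None of these restores the definition. The endpoint as published still depends on an unknown attribution share, and comparing all events by arm does not.

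**Conclusion.** The point holds in this form: the only adverse-event endpoint is limited to study-related events, so the safety comparison between arms depends on a judgement for each event that the randomised, sham-controlled design makes unnecessary. The conclusion rests on the wording of the endpoint and on the premise that events after acute trauma and surgery often have competing explanations.

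Its size is not known. In the 15% against 30% illustration at 123 per arm, power is 81% for all events and ranges from 20% to 97% for the restricted count. At 41 per arm it is 37%, against 10% to 60%. All event rates and attribution shares are assumed. The change is worth making because it is cheap and removes the dependence, not because a loss has been demonstrated.

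**What to change.** In Secondary (exploratory) endpoints and control variables, under Study endpoints, replace the adverse-event item with all adverse events and all serious adverse events by arm, from the intervention to 6 months, regardless of attribution, by CTCAE version 5.0 grade. Give both the number of patients with at least one event and the number of events. Keep study-related events as a subset table, and state that relatedness is judged by an assessor already blinded to allocation. Add adverse-event assessment to the section Blinding and unblinding so that it agrees with Methods.

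The cost is a change of wording, one more table and longer event listings. The sample size, the stopping bounds and the primary analysis are unaffected.

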### Study population

Included are female and male patients with an acute spinal cord lesion regardless of the neurological level of the lesion. Patients with either complete (AIS A) or incomplete (AIS B–D) lesion are included. A minimum age of 18 years must be reached at enrollment. No other age limit was defined. A gender distribution in favor of male patients is expected due to the higher incidence (men/women = 3.8/1) of traumatic SCI [4].

#### Inclusion criteria

Patients with acute traumatic spinal injuries who are awake, responsive, and oriented at admissionPatients from the age of 18 yearsAdmission to hospital within 24 h after injuryWritten consent to participate in the studyParticipation in the Austrian Spinal Cord Injury Study (ASCIS)-Registry (only for the Austrian hospitals)

#### Exclusion criteria

Serious traumatic brain injuries that prevent accurate participation in study procedures and/or adequacy of informed consentParticipation in other interventional clinical trialsSerious concomitant injuries that prevent the neurological initial assessmentPre-existing neurological conditions that affect the primary endpoint of the study and potentially mask or reduce the therapeutic effect of the ESWT applicationHigh-dose administration of corticosteroids such as methylprednisolone, dexamethasone, etc.Complete spinal cord transectionPatients with pacemakers or implantable defibrillatorsPatients who are using devices which are sensitive to electromagnetic radiation(potential) PregnancyPatients with tumorsPatients with severe coagulation disorders

### Study procedures

First, eligibility for study participation will be assessed and informed consent will be obtained in a pre-screening. Additionally, a pregnancy test will be performed in women with childbearing potential prior to the study intervention. After that, eligible patients undergo a baseline examination comprising a short medical history, a neurological examination (AIS/ISNCSCI), radiological imaging, assessment of the presence of pathological reflexes (priapism, plantar reflex), and documentation of pre-operative interventions.

ESWT is applied peri-operatively under general anesthesia (ideally post-operative immediately after skin closure) or within the first 48 h after trauma.

After the study intervention, surgical interventions and intra-operative diagnosis shall be documented. Also, findings from post-operative imaging and the time sequence of the acute care chain are recorded.

The first follow-up exam should be performed as early as 24–72 h after surgery consisting of a comprehensive medical history and drug anamnesis, an assessment of pre-existing neurological deficits, a neurological examination (AIS/ISNCSCI and plantar reflex), a gait analysis, assessment of urological function, rating of injury severity (Injury Severity Score (ISS)), survey of comorbidities (Charlson Comorbidity Index (CCI)), and questionnaires addressing activities of daily life (Spinal Cord Independence Measure (SCIM) and the Walking Index for Spinal Cord Injury II (WISCI II)). Also, a patient diary is handed out to every patient during the first study visit in which patients should record spasms (Penn Spasm Frequency Scale), medication (drug name and dosage), and any important subjective or objective changes in the neurological symptoms.

The 2nd (day 14–21), 3rd (3 months), and 4th (6 months) follow-up visits consist of a neurological examination, a gait analysis, assessment of urological function, and questionnaires addressing activities of daily life. Parameters from routine blood chemistry and changes in medication shall be documented at each study visit. At the last follow-up exam (6 months), the stability of osteosynthesis is re-evaluated according to X-ray/CT, and a copy of the patient diary is filed at the study site.

The study procedures are depicted in a flowchart, as well as in tabular format in the supplementary material.

### Study assessments

#### Concomitant medication

Any medication is documented as part of standard clinical care including dose, duration, and mode of administration. Patients are encouraged to continue their medication after discharge in the prescribed form. If there is a change during the 6-month observation period, this has to be noted in the patient diary, stating the name of the drug, the dosage, and the duration of the intake.

In the study visits 5–8 (follow-up exams 1–4), the following categories of drugs are assessed: NSAIDs, antidepressants, anticonvulsants, opioids, spasmolytics, sedative-hypnotics, neuroleptics, and anticoagulants including drug name and dosage.

The administration of corticosteroids in acute spinal cord trauma is controversial and the indication is discussed in the literature [10, 36–39]. If physicians decide to administer corticosteroids in high dosage, participation in this study is no longer possible for those patients.

No additional medication is administered within the study.

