#### Data analysis

##### Calculation of the composite endpoint

In general, following the intention-to-treat (ITT) approach, all patients are included in the analysis. For scale variables, the means, standard deviations (SD), median values, and minimum/maximum values will be given. For ordinal variables, medians and minimum/maximum values will be calculated and reported. Frequencies and percentages will be given for nominal variables. Missing values are not considered when calculating the percentage.

The International Standards for the Neurological Classification of Spinal Cord Injuries (ISNCSCI) was chosen as the relevant clinical endpoint for this study. This score includes several subscores, which are listed in the table below.

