### Definition of collective analysis

All patients who fulfill the determined inclusion criteria will be used for the data analysis, independent of whether the intended shock wave therapy is performed as planned (intention-to-treat analysis).

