### Handling of missing, unused, or faulty data; drop-outs; and terminations

In order to counteract missing values as best as possible, the study will be carried out according to the GCP principle (Good Clinical Practice). Additionally, a regular evaluation of the collected data will take place. If missing values are detected, an attempt will be made to subsequently determine them and/or to document the reasons.

Missing values concerning the primary endpoint are estimated according to the Last Observation Carry Forward principle (LOCF). If possible, the same procedure is used for the secondary endpoints. In all other cases, an analysis of the observed data will be carried out.

The systematically documented reasons for drop-outs will be evaluated to see if they can be used as a predictor for the endpoints and thereby additional insights into the therapy can be gained.

A sensitivity analysis will be performed in order to estimate the effect of missing data and outliers on the study endpoints.

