## Discussion

Despite extensive efforts in the treatment of SCI, there is yet no causal, curative treatment approach available [10]. The current standard therapy in Austria is the early surgical decompression and stabilization [9, 11, 68] and in some cases the additional administration of steroids (methylprednisolone) in the acute phase of the injury (in the first 24–48 h, the latter being controversial) [10, 36–39].

ESWT is already being used in clinical practice such as chronic wounds, non-healing fractures, tendinopathies, myocardial ischemia, and lithotripsy. The application after acute spinal cord injury would thus be an expansion of indication for this therapy method, which has already been used in Austria for several years [12, 17, 19, 33, 34, 69].

ESWT could provide an easy-to-use, risk-free therapeutic method in the treatment of acute SCI in addition to surgical decompression with the aim of optimizing the clinical outcome.

The underlying study aims to investigate the effect of ESWT after acute traumatic spinal cord injury in humans within 48 h of trauma in order to intervene in the secondary injury phase with the objective to reduce the extent of neuronal damage.

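### The high-dose steroid rule has no time limit, so as worded it can end follow-up of a randomised patient, in tension with the stated intention-to-treat analysis

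*Protocol article*

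**What the plan says.** High-dose corticosteroids appear twice in the protocol article. They are listed under Exclusion criteria, without a time limit. The Concomitant medication section then adds: "If physicians decide to administer corticosteroids in high dosage, participation in this study is no longer possible for those patients". That sentence has no time limit either.

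On timing, the Discussion describes, for some cases in Austria, the "additional administration of steroids (methylprednisolone) in the acute phase of the injury", and dates it "in the first 24–48 h, the latter being controversial". Study procedures says: "ESWT is applied peri-operatively under general anesthesia (ideally post-operative immediately after skin closure) or within the first 48 h after trauma". The first follow-up exam is set at 24–72 h after surgery.

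On blinding, Methods says: "The operating room staff and persons involved in the application of the study intervention are not blinded to group allocation". These staff must keep the allocation secret.

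On the analysis set there are two statements. Calculation of the composite endpoint says that, "following the intention-to-treat (ITT) approach, all patients are included in the analysis". Definition of collective analysis says: "All patients who fulfill the determined inclusion criteria will be used for the data analysis", whether or not the shock wave therapy went as planned. The section on missing data and drop-outs fills a missing primary endpoint by last observation carried forward (LOCF). It also promises an evaluation of drop-out reasons and a sensitivity analysis for missing data.

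**The concern.** An intention-to-treat analysis needs the outcome of every randomised patient, whatever happens after allocation. A rule that ends participation because of a later clinical decision stops that outcome from being collected. The six-month exam is then either absent or replaced by an early score, and randomisation no longer guarantees that the patients with real six-month data are comparable between arms.

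The article calls steroid use in acute spinal trauma controversial, so whether a patient receives them is a matter of judgement and may vary between hospitals and physicians. Some staff near the patient know the allocation. If withdrawal for steroids differed by arm and was related to prognosis, the primary comparison would be biased.

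This is a rule of conduct, so a statistical analysis plan that is not shown here cannot repair it: an examination that was never done cannot be recovered in the analysis.

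**Working it through.** **1. Does the rule reach enrolled patients?** Three features suggest so. The sentence speaks of participation coming to an end. It stands among rules for the six-month observation period. And a pure screening rule would repeat the exclusion criterion already listed. None of these is conclusive.

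**2. Can the steroid decision follow randomisation?** Admission is within 24 h of injury, the intervention is peri-operative or within 48 h of trauma, and steroid use is placed in the first 24–48 h. A patient allocated and treated on day 1 could therefore be given steroids on day 2. The article does not state when randomisation takes place, so this order is possible, not documented.

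**3. What happens to the endpoint?** The endpoint is delta.TMSC = TMSC at 6 months − TMSC at baseline.
- Withdrawn before the first follow-up exam: the last observation is the baseline score, so read literally LOCF gives delta.TMSC = baseline − baseline = 0.
- Withdrawn later: a score from the first days or weeks stands in for the six-month score.

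**4. The plan's own design figure.** Inputs from Study sample size: one-sided alpha 5%, power 80%, p = 0.6, triangular bounds, three stages, 1:1 allocation. For normal data p = 0.6 corresponds to √2 × z(0.6) = 0.358 SD. With u_k = C(1 + k/3)/√k and l_k = C(k − 1)/√k for k = 1, 2, 3, solving for alpha = 0.05 gives C = 1.599. The upper bounds are then 2.13, 1.88, 1.85 and the lower bounds 0.00, 1.13, 1.85. Power is 0.799 with 40 per arm per stage and 0.808 with 41. So 41 × 3 × 2 = 246 reproduces. The bounds as printed give alpha 0.0497 and power 0.807.

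**5. Non-informative loss (assumed rates, no imputation, no replacement).** The sample per arm per stage becomes 41 × (1 − f), for example 41 × 0.9 = 36.9.

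| Removed, f | Power |
|---|---|
| 0 | 0.807 |
| 5% | 0.789 |
| 10% | 0.770 |
| 15% | 0.749 |
| 20% | 0.726 |

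**6. Informative loss if such patients were left out (assumed rates and prognosis).** If removed patients lie g SD below their arm's mean, the bias in the difference is g × [f_T/(1 − f_T) − f_C/(1 − f_C)], with T for treatment and C for control. The sample is held at 41 per arm per stage, so only the bias acts.

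| Control vs treatment removed | g | Bias (SD) | One-sided type I error |
|---|---|---|---|
| 10% vs 10% | 0.5 or 1 | 0 | 0.050 |
| 5% vs 10% | 0.5 | 0.029 | 0.074 |
| 5% vs 15% | 0.5 | 0.062 | 0.110 |
| 5% vs 10% | 1 | 0.058 | 0.106 |
| 5% vs 15% | 1 | 0.124 | 0.214 |

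If the larger share were removed from control, the bias would change sign.

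**7. If they are kept with delta.TMSC = 0.** A share f set to 0 moves the arm mean by −f × m, where m is the mean change those patients would have shown. The documents give no value for m, so this route cannot be sized. Where m is positive, it pulls down the arm with more withdrawals, the opposite direction to step 6. So even the sign of any bias depends on a handling choice that the text leaves open.

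**The case against.** The strongest reply is that the text ends participation but never removes anyone from the analysis. One statement includes all patients. The other turns on inclusion criteria, and high-dose steroids are an exclusion criterion, so a steroid-treated patient still qualifies. LOCF, the evaluation of drop-out reasons and the sensitivity analysis cover the resulting gap. The steroid sentence may also simply restate the screening exclusion.

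Much of this stands. A reader might infer that the rule breaks the intention-to-treat analysis; the documents do not support that, because no section deletes these patients. A reader might also infer that unblinded theatre staff decide on steroids, or that the decision depends on severity. The article says only that physicians decide, and gives neither their blinding status nor their reasons. Finally, a reader might put the bias at about a third of the planned effect: 0.10/0.90 = 0.111 SD, and 0.111/0.358 = 0.31. That needs 10% removed from one arm, none from the other, a prognosis 1 SD worse, and deletion instead of the prescribed LOCF. It is an extreme case of a procedure that the plan does not describe.

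The reply does not remove the gap in timing. The rule has no cut-off at randomisation, and LOCF replaces the missing exam without recovering it.

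**Conclusion.** The point holds in a limited form. As worded, the steroid rule can withdraw a randomised patient before the six-month exam, which conflicts with the aim of both intention-to-treat statements. It rests on reading the rule as reaching enrolled patients and on overlapping time windows.

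Allocation-dependent withdrawal is made possible by staff who know the allocation, but it is not shown. The size is unknown, since no steroid rate is given. An assumed 10% non-informative loss without imputation costs about 4 points of power (0.807 to 0.770). Equal removal with equal prognosis leaves type I error at 0.05. Inflation arises only if removal differs by arm, is related to prognosis, and the patients are left out. This is worth correcting because the lost outcomes cannot be recovered, but it does not by itself invalidate the design.

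**What to change.** Reconcile Exclusion criteria, Concomitant medication, Calculation of the composite endpoint and Definition of collective analysis, so that they state:

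- the steroid criterion governs eligibility before randomisation only, and the moment of randomisation is given;
- a patient who receives high-dose steroids after randomisation stays in the planned follow-up to six months and is analysed in the assigned arm;
- steroid use after randomisation is recorded and used in a sensitivity analysis. Medication is already documented in general, but corticosteroids are not among the drug categories listed for follow-up exams 1–4, so they should be added;
- the analysis set is all randomised patients, in place of those who meet the inclusion criteria.

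This concerns follow-up and analysis only. It changes no treatment decision and takes no position on steroid use.

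The cost is a protocol clarification and the continuation of already planned visits for a few patients. The statistical downside is that steroid use may add some noise or dilute the effect; the sensitivity analysis is there to show how much.
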